### Blinding

2.10

Patients and researcher team will remain blinded to complete treatment period of 3 months. Treatment allocations will only be revealed at the end of study. The placebo capsule is similar to the study drug for taste, color, size and both of supplements manufacture with identical company (Shahdineh Golha pharmaceutical Company, Isfahan, Iran).

### Applied tests during the study

2.11

#### Medical interview

2.11.1

At baseline and after the 3 months intervention, we will assess patients and collect data of the number of tender and swollen joints on the basis of the 28-joint count, Visual Analogue Scale (0–100 mm) for DAS-28 and pain.

### Assessment of anthropometric measurements

2.12

Weight and height will be measured at the beginning and the end of the study without shoes and minimal clothing by a trained attendant. BMI will be calculated using the height and weight measurements (weight in kg/[squared height in meters]). WC will be measured at the midpoint of the lowest rib and iliac crest.

### Laboratory assessment

2.13

Seven ml of venous blood will be obtained from all of patients after 10–12 h fasting at the beginning and after 3 months of intervention in the Sadra lab. The serum and plasma will be separated by centrifugation at 3000 rpm for 10 min, then the serum samples will be stored at −70 °C after centrifugation until assay. Finally, Serum hs-CRP, SOD, CAT, GPx, TNF-α, IL-17, TAC, and TOS concentrations will be quantified by the use of a commercial ELISA kit. Spectrophotometric method will be used to determine serum MDA by using the thiobarbituric acid reactive substance method [28]. Serum levels of triglycerides (TG), total cholesterol (TC), and high-density lipoprotein cholesterol (HDL-C) will be measured enzymatically. Low-density lipoprotein cholesterol (LDL-C) will be calculated by the Friedwald formula as follows [29]:

LDL cholesterol = (Total cholesterol-HDL cholesterol) – (Triglyceride/5)

### Statistical methods

2.14

All our analyses will be based on the intention-to-treat (ITT) approach. Data will be analyzed by using the SPSS software, version 23 (SPSS Inc, Chicago, IL, USA). Quantitative data will be presented as mean ± standard deviation (SD), and qualitative data are will demonstrated as frequency and percent. The Kolmogorov-Smirnov test will be used to assess the normality of data. Paired *t*-test will be used for before and after intervention comparisons. Analysis of covariance (ANCOVA) will be applied to identify any differences between two treatment groups after adjusting for confounding variables. Results will be considered statistically significant at p-value less than 0.05.

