**Methods/design:**

Randomized, placebo-controlled, and double-blind clinical trial aiming to recruit 48 patients with RA. Block randomization will be used. An intervention group will receive 500 mg/twice a day propolis capsules for 3 months and control group will receive the placebo for the same dose and duration. The oxidative stress status (malondialdehyde (MDA), total antioxidant capacity (TAC), total oxidant status (TOS), superoxide dismutase (SOD), catalase (CAT), glutathione peroxidase (GPx)), and inflammatory biomarkers (interleukin-17 (IL-17), Tumor necrosis factor alpha (TNF-α), High-sensitivity C-reactive protein (hs-CRP)), lipid profile (total cholesterol (TC), high density lipoprotein (HDL-c), low density lipoprotein (LDL-c), and triglyceride (TG)) and also physical activity, anthropometric indices, clinical and nutritional status will be measured at beginning and end of this study. The primary analysis will be based on theintention-to-treat principle.

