### Safety consideration

2.8

During the screening and follow-up any abnormalities detected will be discussed with rheumatologist involved in the study. Also, if we see any side effects after consumption of propolis, the patient will be excluded from the study. All participants will be informed of their blood test results as the study will be completed.

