### Power calculation and sample size estimates

2.9

To determine the sample size in this study, we used the previous study [27]. Also, we used from sample size formula suggested for randomized clinical trials. We considered the Type I error of 5% (α = 0.05) and Type II error of 20% (β = 0.2; power = 80%) and serum levels of MDA as a primary outcome, and we calculated the sample size of 18 persons for each group. With 30% dropout, finally twenty-four patients will consider for each group.

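### Section 2.8 removes randomised women with side effects from the study, while Section 2.14 and the Abstract promise intention-to-treat analysis

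*Protocol article*

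**What the plan says.** Section 2.14 (Statistical methods) makes a general commitment: "All our analyses will be based on the intention-to-treat (ITT) approach". The Abstract repeats it for the main result: "The primary analysis will be based on" the intention-to-treat principle.

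Section 2.8 (Safety consideration) deals with a woman who has side effects after taking propolis: "the patient will be excluded from the study". It states no threshold for the side effect, and it does not say whether she is still to be seen at 3 months.

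Section 2.13 (Laboratory assessment) plans blood "after 10–12 h fasting at the beginning and after 3 months of intervention". Section 2.11.1 sets the same two times for the joint counts and visual analogue scale, and Section 2.16 defines the DAS28 and HAQ outcomes as changes over 3 months. No intermediate outcome measurement is described.

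Two outcome analyses are named in Section 2.14. Within groups, a paired t-test: this "test will be used for before and after intervention comparisons". Between groups: "Analysis of covariance (ANCOVA) will be applied to identify any differences between two treatment groups after adjusting for confounding variables".

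**The concern.** Intention-to-treat means that every randomised woman stays in her allocated group for follow-up and analysis, whatever happens to her treatment. Removing a woman because of an event that may be caused by the capsules is the kind of post-randomisation selection that the principle is meant to prevent.

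In this design the removal also costs the data. With one follow-up time, a woman who leaves early never gives a post-baseline value for MDA, IL-17, TNF-α, TAC, TOS, DAS28 or HAQ. A later analysis plan can choose how to impute such values, but it cannot recover a sample that was never drawn.

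What is at stake is the randomised comparison. If side effects are more common in one arm, and the women who have them would have had different results, the remaining groups are no longer comparable. The report would still carry the ITT label, and a reader would have no reason to look for the problem.

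**Working it through.** **The sections set side by side**

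1. Section 2.14 and the Abstract: all randomised women count, in all analyses.
2. Section 2.8: a randomised woman with side effects leaves the study.
3. Sections 2.11.1 and 2.13: outcomes exist at baseline and 3 months only. From 2 and 3, a woman who leaves before 3 months has no outcome.
4. Section 2.14: the paired t-test needs both values from each woman, and ANCOVA needs the 3-month value. From 3 and 4, she contributes nothing to either unless a value is imputed.
5. So following Section 2.8 as written leaves the commitment in 1 without observed outcomes for these women, for a reason tied to treatment.

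**Are the losses likely to be equal between arms?** Section 2.8 names propolis only. Section 2.10 keeps patients and researchers blinded, so in practice the rule could only be applied to capsules in general. The loss would then be equal only if corn-starch placebo and propolis led to the same side effects. The document gives no side-effect rates for either.

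**Scale of loss.** The only figure available is the dropout allowance in Section 2.9: "With 30% dropout, finally twenty-four patients will consider for each group". It is reproduced by 18 × 1.30 = 23.4, rounded up to 24. Thirty per cent of 24 is 7.2 women per arm, or 14.4 of 48. That allowance is not tied to side effects, so I use 30% as the top of a range and not as a forecast of removals under Section 2.8.

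**Size of a possible bias.** Let p be the share of an arm lost, and δ the amount, in SD, by which the lost women would have done worse than those retained, after baseline adjustment.

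- The mean of the full arm is (1 − p) × retained mean + p × lost mean, so the retained women look better than the full arm by p × δ.
- Bias in the comparison, in favour of propolis = p(propolis) × δ(propolis) − p(placebo) × δ(placebo).

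With the same δ in both arms:

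| Lost, propolis | Lost, placebo | δ = 0.25 | δ = 0.5 | δ = 1.0 |
|---|---|---|---|---|
| 10% | 0% | 0.025 SD | 0.05 SD | 0.10 SD |
| 30% | 0% | 0.075 SD | 0.15 SD | 0.30 SD |
| 30% | 10% | 0.05 SD | 0.10 SD | 0.20 SD |
| 30% | 30% | 0 | 0 | 0 |

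For example, 0.30 × 0.5 = 0.15, and (0.30 − 0.10) × 0.5 = 0.10. Every p and δ in the table is an assumption.

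**The case against.** **Exclusion may mean only that capsules are stopped.** Section 2.8 does not say that the woman's data are deleted, and Section 2.13 plans blood from all patients at both times. On that reading there is no conflict. This is fair, and it may be what was meant. But the words are exclusion from the study, and no section says that excluded women return at 3 months. The text has to be settled one way or the other.

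**The missing-data method belongs in the analysis plan.** This stands. A reader might infer that the named analyses discard every woman without a 3-month sample. The document does not say so. Complete-case deletion is a software default and not a rule in this protocol, and both methods can be run on imputed data. Silence on imputation in a condensed article is not a fault. The point rests on what Section 2.8 does say.

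**Planning for dropout contradicts ITT.** A reader might also infer this from Section 2.9. It does not follow. Raising the sample size for expected loss is ordinary practice and does not define who is analysed.

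**The bias could be expressed as a share of the planned effect.** It is tempting to divide the figures above by the effect implied by 18 per group. The document gives no effect size or SD, so that effect has to be back-solved. The larger figures also assume loss in one arm only. Such percentages are not an expected size.

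**A mixed model on all 48 women would solve it.** It would not. With one baseline and one follow-up value, and only follow-up missing, a common-baseline likelihood model gives essentially the same treatment estimate as baseline-adjusted ANCOVA in the women with 3-month data. The remedy has to come mainly from collecting the outcome.

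**Conclusion.** The concern holds in a limited form. Section 2.8 and the ITT statements in Section 2.14 and the Abstract conflict as written and must be reconciled. Because there is a single follow-up time, the conflict affects which outcomes exist at all, so it cannot be left wholly to an analysis plan.

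The conclusion rests on reading exclusion from the study as the end of follow-up, which is the plain sense of the words. The size is unknown. It is zero if loss and prognosis of the lost women are alike in both arms, and up to 0.30 SD in the most one-sided scenario shown. The document gives no side-effect rates by which to choose between these. It does not support a claim that the planned analyses are by rule completer analyses, or that the sample size shows this.

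The correction should be made. It is cheap and removes an avoidable source of bias, but the point does not by itself invalidate the trial.

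**What to change.** 1. Reconcile Section 2.8 with Section 2.14 by separating two decisions: stopping capsules and leaving follow-up. When capsules should be stopped is a clinical matter on which this review takes no position.
2. State that the scheduled 3-month blood sample and DAS28/HAQ assessment will be taken from every randomised woman who consents, whether or not she still takes capsules, and that she is analysed in the group to which she was randomised.
3. Add one sensitivity analysis in which 3-month values still missing in the propolis arm are filled in and then shifted in the unfavourable direction, for example by 0.25 to 1 SD (an assumed range). The estimate moves by the share missing times the shift: two of 24 missing and a 1 SD shift move it by 2/24 = 0.083 SD.
4. If these women will not be followed, replace the ITT wording in the Abstract and Section 2.14 with a description of the analysis as one of women with 3-month data.

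**Cost:** a few sentences of amendment, some recall visits within the existing schedule, and a little more analysis. Recruitment had already begun when the article was written, so the change is worth making promptly: a woman removed earlier can still give a 3-month sample only if she agrees and that date has not passed.

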**Discussion:**

If this randomized clinical trial shows the reduction in inflammatory cytokines and oxidative stress and improves clinical outcome, it would provide evidence for other clinical trials to evaluate the efficacy of propolis supplementation in RA patients.

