### Inclusion criteria

2.3

-Diagnosis of the disease by a rheumatologist based on the criteria of the American College of Rheumatology [25].-Women in the age range of 20–70 years.-Identical drug advisement during study in both of groups.-Patients with moderate and severe disease activity-Participants with a history of antioxidant supplements use in three months leading to the study were also excluded-The tendency to cooperate and sign informed written consent

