### Outcome measures

2.15

The primary outcome of this trial is the change in serum levels and inflammatory (IL-17, TNF-α, TAC ، TOS, and MDA markers between two groups.

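### Section 2.14 plans before-after paired t-tests under the same p<0.05 rule as the between-group ANCOVA, although every listed outcome is a between-group comparison

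*Protocol article*

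**What the plan says.** Section 2.14 (Statistical methods) names two inferential procedures. A paired t-test "will be used for before and after intervention comparisons". ANCOVA "will be applied to identify any differences between two treatment groups after adjusting for confounding variables". One unqualified sentence closes the section: "Results will be considered statistically significant at p-value less than 0.05". The paired tests are not called descriptive. The arm in which they are run is not named. Within each arm is the natural reading; pooling the two arms would say even less about propolis.

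The outcomes are defined as contrasts between groups. Section 2.15 gives the primary outcome as the change in "markers between two groups", and each of the four secondary outcomes in section 2.16 is a comparison of changes in the two groups.

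Two other places bear on the point. Section 2.3 admits "Patients with moderate and severe disease activity", and section 2.6 has participants continue their usual medication. The Discussion paragraph of the abstract looks ahead with the words "If this randomized clinical trial shows the reduction in inflammatory cytokines and oxidative stress and improves clinical outcome".

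**The concern.** A before-after test in one arm asks whether that arm changed. The trial asks whether the arms changed by different amounts. Usual treatment, placebo response and regression to the mean can move both arms together, and a paired test in the propolis arm attributes none of this to its source.

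Regression to the mean bears most directly on DAS 28, because patients are selected on disease activity. For MDA, TAC, TOS, IL-17 and TNF-α it could act only through their correlation with disease activity, for which the article gives no figure.

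What is at stake is interpretation. Under section 2.14 a within-arm p-value below 0.05 would be declared significant on the same footing as the randomised comparison. A result significant in propolis and not in placebo invites the conclusion that the arms differ, which that pair of p-values does not show. Much of the article's language about success speaks of reduction or improvement without saying relative to placebo, which makes the slip easier.

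**Working it through.** **Inputs from the article.** 18 evaluable and 24 enrolled per group, 30% dropout (section 2.9); 1:1 allocation (section 2.6); significance at 0.05 (section 2.14, sidedness not stated, taken here as two-sided).

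**Assumptions.** The same mean change in both arms and no propolis effect; normal data; independent arms. The shared change is expressed as d, the mean change divided by the SD of the change scores, at 0, 0.3, 0.5 and 0.8. The ANCOVA simulation also assumes a baseline to follow-up correlation of 0.5. The article gives no expected change, SD or correlation, so none of these values comes from it.

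**The plan's own figure.** 18 × 1.30 = 23.4, rounded up to 24, matches the stated number per group (18 / 0.70 = 25.7 would give 26). The 18 itself cannot be reproduced, because no MDA difference or SD is printed. Both sizes serve below only as the likely range of patients analysed per arm.

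**Step 1, paired test in the propolis arm.** The chance of a significant improvement is P = Pr[T > t(0.975; n−1)], where T is noncentral t with n−1 degrees of freedom and noncentrality d√n. For n = 18 and d = 0.5, the noncentrality is 0.5 × √18 = 2.12 and the critical value is 2.11, which gives P = 0.516.

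**Step 2, significant in propolis only.** With independent arms this is P × (1 − Q), where Q is the two-sided chance of significance in the placebo arm. For n = 18 and d = 0.3, where Q is practically equal to P, it is 0.224 × 0.776 = 0.174. Because Q is at least P, the product cannot exceed P(1 − P) = 0.25 − (P − 0.5)², so 25% is a ceiling.

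**Step 3, between-group ANCOVA adjusted for baseline.** Simulated with 20,000 runs per row. A shift common to both arms is absorbed by the intercept, so the test of the group term should not depend on d.

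| n per arm | d | d√n | Propolis paired test significant (improvement) | Significant in propolis only | ANCOVA significant (either direction) |
|---|---|---|---|---|---|
| 18 | 0 | 0 | 2.5% | 2.4% | 5.1% |
| 18 | 0.3 | 1.27 | 22.4% | 17.4% | 4.8% |
| 18 | 0.5 | 2.12 | 51.6% | 25.0% | 4.7% |
| 18 | 0.8 | 3.39 | 89.2% | 9.6% | 4.9% |
| 24 | 0 | 0 | 2.5% | 2.4% | 4.7% |
| 24 | 0.3 | 1.47 | 29.1% | 20.6% | 5.0% |
| 24 | 0.5 | 2.45 | 65.0% | 22.7% | 4.6% |
| 24 | 0.8 | 3.92 | 96.3% | 3.5% | 5.0% |

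The paired-test columns count improvement only, whereas the ANCOVA column counts both directions. By symmetry about half of the latter, some 2.5%, would favour propolis. A larger sample makes the paired test more likely to detect the shared change and leaves the ANCOVA rate where it is.

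**The case against.** The strongest reply is that the article already gives the efficacy question to the right test. The sentence after the paired t-test assigns treatment-group differences to ANCOVA, and sections 2.15 and 2.16 frame every outcome as a between-group contrast. This stands. A reader might infer that the plan will present improvement common to both arms as a propolis effect. The documents do not support that: no section says a within-arm change will be taken as evidence of efficacy, and the abstract's sentence on reduction is a forward-looking remark about a placebo-controlled trial, with no success criterion and no mention of a within-arm test.

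It is also fair to say that the percentages are conditional. The shared changes are assumed; with no shared change the propolis paired test shows improvement only 2.5% of the time. The 25% for significance in propolis only is the mathematical maximum and not a typical value. All these rates become rates of false claims only if someone reads the paired test as an efficacy result.

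Finally, one may say that the role of the paired tests is detail left to a full protocol or SAP that is not shown. This part does not hold. The point does not rest on something left out. Section 2.14 states a test, places it under the general significance rule, and the test matches none of the outcomes the article lists.

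**Conclusion.** The point holds as a mismatch between a stated analysis and the stated outcomes, and as a matter of wording. The paired t-tests address no outcome in sections 2.15 and 2.16, cannot isolate propolis from change common to both arms, and still fall under the 0.05 rule. The between-group ANCOVA remains a suitable comparison, and nothing here touches its validity or the sample size.

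For shared changes of 0.3 to 0.5 SD with no propolis effect, the propolis paired test would be significant about 22% to 52% of the time at 18 per arm and 29% to 65% at 24. These figures rest on assumed changes and on normal, independent arms. They illustrate the hazard of reading the paired tests as efficacy evidence; they are not the error rate of the planned between-group analysis.

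**What to change.** In section 2.14, replace the paired t-tests with a summary of within-arm change as mean change with SD or 95% CI, without p-values. If the authors wish to keep the tests, label them descriptive only and exempt them from the significance rule. Add one sentence stating that all efficacy conclusions, including any statement in the abstract or discussion that propolis reduces a marker or improves a clinical score, rest on the between-group ANCOVA estimate and its 95% CI.

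The cost is a few lines of text and slightly less analysis. Data collection, sample size, outcomes and trial conduct stay as they are.

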### Outcome measures

2.15

The primary outcome of this trial is the change in serum levels and inflammatory (IL-17, TNF-α, TAC ، TOS, and MDA markers between two groups.

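### The sample size is set on serum MDA alone, but section 2.15 names five unranked primary markers, so the stated 5% error and 80% power hold only for an MDA-only primary

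*Protocol article*

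**What the plan says.** Three sections of the protocol article bear on this.

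- **Section 2.9 (Power calculation and sample size estimates)** sets a "Type I error of 5% (α = 0.05") and a "Type II error of 20% (β = 0.2; power = 80"%), and continues: "serum levels of MDA as a primary outcome, and we calculated the sample size of 18 persons for each group". This is raised to 24 per group for dropout. No other outcome enters the calculation.
- **Section 2.15 (Outcome measures)** speaks of one primary outcome in the singular but lists five: "The primary outcome of this trial is the change in serum levels and inflammatory (IL-17, TNF-α, TAC", and then "TOS, and MDA markers between two groups". It gives no order, no composite, and no statement of how many markers must show an effect.
- **Section 2.14 (Statistical methods)** compares the groups by ANCOVA and sets one threshold: "Results will be considered statistically significant at p-value less than 0.05".

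Section 2.16 lists DAS28, HAQ, the antioxidant enzymes and the lipid profile as secondary. The four markers other than MDA therefore stand as primary and nowhere else.

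**The concern.** A sample size calculation is a statement about one hypothesis test, or one defined set of tests. Here the calculation is for one marker at 0.05, while the outcome definition has five markers of equal standing, each to be read against the same 0.05. The two sections do not describe the same primary analysis.

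At stake is what a positive trial would mean. With five equal primaries and no stated decision rule, a report could rest its primary claim on whichever marker crosses the threshold, or could require all of them. The planned error rates fit neither case. The article's Conclusion says the result may inform policy on propolis use in RA, so the claim should rest on an analysis whose error rates are known.

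**Working it through.** **Inputs from the article.** Alpha 0.05, power 80%, 18 per group and 24 after dropout (2.9); 1:1 allocation (2.6); five primary markers (2.15); threshold 0.05 (2.14).

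**Inputs not in the article, assumed here.** Two-sided tests; the correlation between markers (shown as a range); the MDA difference and SD (solved back from the stated 18 and 80%).

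**1. The plan's own figure.** The 18 per group cannot be reproduced directly, because the article cites a previous study but gives no MDA difference or SD. Solving back for the standardised difference d that gives 80% power:

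- Normal approximation: d = √(2 × (1.960 + 0.842)² / 18) = 0.934.
- Two-sample t-test: d = 0.961.

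The step to 24 is 18 × 1.3 = 23.4, rounded up. It does not affect this point.

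**2. Reading A: any one of the five markers is enough.** Chance of at least one false positive when propolis affects none of them:

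- Upper bound under any dependence: 5 × 0.05 = 25%.
- Independent tests: 1 − 0.95⁵ = 22.6%.
- Equal positive correlation, by simulation of five two-sided tests (1,000,000 runs each): 20.9% at 0.3, 18.3% at 0.5, 14.9% at 0.7, about 10% at 0.9.
- Perfect correlation: 5%.

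**3. Reading B: all five markers are required.**

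- The false-positive rate is at most 5%, since every test must pass at 0.05.
- Joint power, if the tests are independent and each has 80%: 0.8⁵ = 32.8%. Positive correlation would raise this, but never above the power of the weakest marker. The article states no power for four of the five.

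**4. Reading C: MDA alone is primary.** Alpha is 5% and power 80% at 18 evaluable per group, as section 2.9 states. This is the only reading under which both figures hold.

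**5. Cost of keeping five primaries with error control.** With Bonferroni, or at the first step of Holm, each marker is tested at 0.05 / 5 = 0.01. Power for MDA at 18 per group:

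- Normal approximation: Φ(0.934 × √(18/2) − 2.576) = Φ(0.226) = 58.9%.
- Two-sample t-test with d = 0.961: 56.6%.

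Restoring 80% for MDA at 0.01 needs 2 × (2.576 + 0.842)² / 0.934² = 26.8, so 27 evaluable per group instead of 18; the t-based calculation also gives 27. Under Holm, 57–59% is a floor for MDA, because its threshold loosens if other markers are rejected first.

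**The case against.** The strongest objection is that section 2.9 calls MDA *a* primary outcome, not the only one, and MDA is in the list in 2.15. On that reading the sections are compatible: the trial has several primaries and was sized on one of them. The indefinite article is a fair point, and the text does not declare MDA the sole primary. But this does not rescue the stated figures. Four primaries are left without any power statement, and the 5% is left without a defined meaning for the set.

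A reader might infer that the trial carries a 23% chance of a false positive. The article does not support that as a flat statement. It needs independent tests, although the five markers come from the same patients and TAC, TOS and MDA all belong to the oxidative stress set, so some correlation is likely. It also needs a rule that one marker suffices, which appears nowhere. The Abstract's Discussion and section 3 word the hoped-for result jointly, as improvement in inflammation and oxidative stress together. That is not a formal decision rule, but it does not favour an any-one reading.

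A multiplicity method or success rule may properly sit in an analysis plan that is not shown, and the threshold sentence in 2.14 does not rule out adjusted p-values. The absence of such a rule is therefore not the finding. The mismatch between 2.9 and 2.15 is, and a separate plan would not make those two sections agree.

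A reader might also count the absence of "High-sensitivity C-reactive protein (hs-CRP") from both outcome lists as part of this fault. It is a side issue: a measured variable need not be a listed outcome, the sentence in 2.15 is visibly garbled, and the error rates here do not depend on it.

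Finally, the power figures in step 5 are back-solved using a simple two-group comparison, whereas the planned test is ANCOVA. They show the order of the loss, not an exact value.

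**Conclusion.** The concern holds as a mismatch between sections 2.9 and 2.15. The 5% and 80% of section 2.9 apply only if MDA is the single primary outcome, and section 2.15 as written says otherwise.

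The size depends on a decision rule that the article does not state. If any one marker counts, the error exceeds 5% unless the markers are perfectly correlated, and the 15–21% range rests on assumed correlations. If all five must succeed, the error is controlled and the loss falls on power; the 33% rests on independence and on granting 80% to each marker. The contradiction itself needs none of these assumptions. It should be resolved before unblinding, because a choice among five markers made afterwards would be open to the charge of selection.

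**What to change.** By a dated amendment before allocations are revealed:

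- In 2.15, name one primary outcome that matches 2.9: the between-group difference in serum MDA at 3 months, adjusted for baseline, at two-sided 0.05.
- Move IL-17, TNF-α, TAC and TOS to the secondary outcomes in 2.16.

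If all five are to stay primary, apply Holm across them and replace the 80% with the power that this leaves: about 57–59% for MDA at 0.01 with 18 per group, as back-solved above. Give the power for the other four as well.

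**Cost.** The first option needs no extra patients or assays. It is still a substantive change, since the trial is registered and recruiting, so it must be dated and justified. The registry record is not at hand and should be checked and aligned. The scientific price is that a lone significant cytokine could no longer be called a positive primary result. The second option keeps that possibility, at the cost of lower power or a larger trial.
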